## Abstract

**Background:**

In metastatic colorectal cancer (CRCm), fatigue is pervasive, reduces quality of life, and is negatively associated with survival. Its course is explained in part by psychosocial variables such as emotional distress, coping strategies, or perceived control. Thus, to reduce fatigue, psychosocial interventions appear to be relevant. In some cancers, Cognitive Behavioral Therapies (CBT) reduce fatigue. Hypnosis is also used as a complementary therapy to reduce the side effects of cancer. While CBT requires specific training often reserved for psychologists, hypnosis has the advantage of being increasingly practiced by caregivers and is therefore less expensive (Montgomery et al., 2007). On the other hand, CBT and hypnosis remain understudied in the CRC, do not focus on the symptom of fatigue and in Europe such programs have never been evaluated.

**Objectives:**

Implementing an intervention in a healthcare setting is complex (e.g., economic and practical aspects) and recruiting participants can be challenging. The primary objective will therefore be to study the feasibility of two standardized interventions (hypnosis and CBT) that aim to reduce fatigue in patients with CRCm treated in a French cancer center.

**Methods and design:**

A prospective, single-center, randomized interventional feasibility study, using mixed methods (both quantitative and qualitative). A total of 60 patients will be allocated to each intervention group [Hypnosis (*n* = 30) and CBT (*n* = 30)]. Participants will be randomized into two parallel groups (ratio 1:1). Both programs will consist of 6 weekly sessions focusing on the CRF management over a period of 6 weeks. Trained therapists will conduct the program combining 3 face-to-face sessions and 3 online sessions. The feasibility and experience of interventions will be evaluated by the outcome variables, including the adhesion rate, the reasons for acceptability, relevance or non-adherence, the satisfaction, the fatigue evolution (with ecological momentary assessments), and the quality of life. All questionnaires will be self-assessment using an online application from the cancer center.

**Discussion:**

Results will highlight the barriers/facilitators to the implementation of the program and the relevance of the program to the patients, and will be used to generate hypotheses for a randomized control trial.

**Clinical trial registration:**

ClinicalTrials.gov Identifier: NCT04999306; https://clinicaltrials.gov/ct2/show/NCT04999306.

## Introduction

In cancer patients, fatigue appears to be one of the most frequent and persistent symptoms (NCCN National Comprehensive Cancer Network, 2017). Cancer-related fatigue (CRF) has been defined as a distressing, persistent, subjective sense of physical, emotional, and/or cognitive tiredness or exhaustion related to cancer and/or cancer treatment that is not proportional to recent activity and interferes with usual functioning (NCCN National Comprehensive Cancer Network, 2017). Patients consider it severe and intense (Stone et al., 2000). Fatigue can have important psychosocial consequences such as reduced daily activities, and decreased quality of life (Lawrence et al., 2004; Forlenza et al., 2005).

Patients with metastatic colorectal cancer (CCRm) may follow several chemotherapy cycles. They follow months or even years of treatments, leading to many side effects (Wagland et al., 2015) and involving a decrease in Quality of Life (QoL) and functional status (Mayrbaeurl et al., 2016). In patients with colorectal cancer, fatigue ranks first among chemotherapy-related adverse events, with 75% of patients presenting a grade 3-4 with physical and psychological consequences (Mitry et al., 2010; Mota et al., 2012; Vardy et al., 2014). Then, metastatic progression and the increasing number of treatments are also aggravating factors (Peria et al., 2012), with a study reporting that 16% of patients in a clinical trial have fatigue graded at ¾, which corresponds to a very intense fatigue (Miyamoto et al., 2016).

CRF is not only a consequence of the disease or the treatments. Indeed, some authors have made recommendations for psycho-oncology researchers to study the role of personality in developing or coping with CRC cancer and the associated QoL (Sales et al., 2014). To better understand the psychological factors associated with fatigue in CRCm patients, a recent study highlighted distinct trajectories of fatigue in this specific population during the course of chemotherapy (Baussard et al., 2022). That study was theoretically based on the Transactional, Integrative and Multifactorial (TIM) model (Bruchon-Schweitzer and Boujut, 2014) which suggests that health issues are explained by sociodemographic, medical and dispositional variables (such as personality) and by contextual variables (such as resources, e.g., coping strategies, perceived control, etc.). As shown in Figure 1A, Baussard (2018) have applied this model to the specific CRF and its evolution during the treatment. Results suggest that in CRCm patients undergoing chemotherapy, four distinct fatigue profiles were identified. The probability of belonging to each of these trajectories is explained by variables considered by the TIM model: tired patients are those reporting more emotional distress, little perceived control or inadequate coping strategies (Baussard et al., 2022). These results corroborate the literature underlying the relationship between emotional distress and fatigue (Blesch et al., 1991; Mols et al., 2012; Yennurajalingam et al., 2016), even in CRC patients (Mota et al., 2012; Tung et al., 2016). To our knowledge, it remains, however, the only study that have investigated psychological resource variables (such as coping, perceived control, etc.), suggesting that fatigue may be a consequence of a psychological maladjustment and imply that psychosocial interventions may be proposed to patients.

**Figure 1 F1:**
[figure not shown]
**(A,B)** From theory to practice–psychosocial interventions (CBT and hypnosis) applied to the determinants of cancer-related fatigue.

To address fatigue in cancer patients, the NCCN National Comprehensive Cancer Network (2017) highlights several types of interventions such as physical activity and psychosocial interventions. In 2008, Kangas et al. conducted a meta-analysis using data from 57 studies of non-medication therapies in cancer. The results indicated that the most effective strategies were physical activity and psychosocial interventions such as Cognitive and Behavioral Therapies (CBT), with no major difference in effectiveness between these two types of intervention (Kangas et al., 2008; Mustian et al., 2017). CRC patients reported barriers to physical activity programs, including age, pain, or respiratory and cardiovascular comorbidities (Fisher et al., 2016). Thus, we believe that psychosocial interventions have value and another meta-analysis in breast cancer patients reported that, like exercise programs, CBT, relaxation, counseling and hypnosis are beneficial in improving fatigue among patients with breast cancer (Duijts et al., 2011).

CBT for cancer patients includes therapeutic strategies focused on stress management (e.g., related to the announcement, surgery, treatment), problem solving to better cope with difficult situations, or cognitive restructuring (e.g., modification of dysfunctional cognitions associated with cancer) (Page et al., 2006; Berger et al., 2009; Chaloult et al., 2010; Cousson-Gélie et al., 2011). As shown in Figure 1B, CBT could be applied directly to CRF, by working on the thoughts and cognitive distortions associated with the symptom of fatigue. It aims to reduce emotional distress and encourage the development of a sense of control. Müller et al. (2021) found that increased self-efficacy and decreased fatigue catastrophizing, focusing on symptoms, perceived problems with activity and depressive symptoms mediate the reduction of fatigue brought by CBT. Finally, many studies have shown the effectiveness of CBT on fatigue in cancer patients (Page et al., 2006; Berger et al., 2009; Morin et al., 2009; Heckler et al., 2016) but never in patients undergoing chemotherapy for a metastatic CRCm.

In addition, the French Academy of Medicine suggest the interest of medical hypnosis in the management of the side effects of chemotherapy, such as nausea, vomiting or CRF (Bontoux et al., 2013). Hypnosis is defined as “a state of consciousness involving focused attention and reduced peripheral awareness characterized by an enhanced capacity for response to suggestion” (Elkins et al., 2015). Studies in breast cancer patients show a positive effect of hypnosis combined with CBT on symptoms of distress and physical fatigue (Cramer et al., 2015; Roe et al., 2016). A recent literature review found that only six studies investigated the effectiveness of hypnosis (not combined with another therapy) on cancer symptoms and CRF (Baussard et al., 2020). Results indicate that four studies reported effectiveness of hypnosis: two studies when the session is conducted by a therapist (Montgomery et al., 2007; Jensen et al., 2012), with effect sizes (*d*) equal to 0.80 and 2.05 respectively, and two studies reported significant efficacy of auto-hypnosis (listening audio-tape) (Bragard et al., 2017; Gregoire et al., 2017). However, these four studies remain in the minority and have limitations in generalizing the results. First, the samples are too small with *n* = 8 in the study by Jensen et al. (2012) and *n* = 68 for the studies by Bragard et al. (2017) and Gregoire et al. (2017). Second, all of these studies focused on women with breast cancer, which is a specific population. The study of Montgomery et al. (2007), a two-arm RCT with *n* = 100 for the hypnosis intervention seems more robust but assessed post-surgery fatigue, which again is very specific. Thus, this review of the international literature concludes that there is a lack of studies on the effectiveness of hypnosis for CRF (Baussard et al., 2020).

As shown in Figure 1B, as well as CBT, hypnosis could be used to manage CRF, by suggesting ways to regain energy or rest, or by working on a “safe place” to enhance relaxation, etc. The aim is to modify the patient's representations and to help her/him to tame this symptom. In addition, hypnosis has the advantage of being increasingly practiced among professional caregivers in hospitals (Montgomery et al., 2007; Gueguen et al., 2015), and also accepted by the patients (Bragard et al., 2017) which facilitates its implementation.

Thus, the relative efficacy of hypnosis and CBT on CRF has been described in oncology, but very few of these interventions have been conducted specifically on CRCm patients. The difficulties in implementing such programs in the care pathway underlines the importance of conducting this type of study. To our knowledge, there is no study proposing CBT or hypnosis in patients with CRC to reduce CRF. Since the implementation of two psychosocial intervention programs in a health care center is complex, and there is a need to develop standardized interventions for a specific population (CRCm patients), it was decided to first conduct a feasibility study. van Lankveld et al. (2018) suggest that feasibility studies should assess interest and willingness of patients to receive professional psychosocial care. To go further, evidence-based practice, defined as “the conscientious, explicit and judicious use of current best evidence in making decisions about the care of individual patients” (Trinder, 2008) has become an important feature of health care systems and health care policy.

Furthermore, several studies and meta-analyses underline a better effectiveness of face-to-face sessions (Montgomery et al., 2002; Schnur et al., 2008; Askay et al., 2009), and individual sessions rather than group sessions (Cousson-Gélie et al., 2011). We therefore propose individual face-to-face sessions. Beside, the programs in this study are intended to respect the chemotherapy pathway of CRC patients (i.e., a treatment every 2 weeks). This approach seems to be essential to allow a good implementation within the hospital, and not to induce an additional fatigue in patients by imposing them an additional travel.

This will also allow us to gather precise indicators (barriers/facilitators) regarding the implementation of psychosocial interventions in cancer centers, in order to meet the expectations of an increasingly personalized medicine, insisting on the essential place of support care.

### Objectives

The main objective will be to assess the feasibility of two standardized interventions for fatigue reduction in patients with CCRm. One of the two interventions will propose a dedicated CBT and the other an hypnosis intervention. It seems essential to assess the proportion of volunteers to participate in these interventions as well as the acceptability of the programs, the method of data collection and the barriers/facilitators to the implementation of these two interventions. Therefore, several secondary objectives are planned:

To assess acceptance to participate in the study and reasons for refusal;To identify the reasons for non-adherence to the program;To highlight the barriers/facilitators to the implementation of the protocol;To evaluate the relevance of the program (adapt to the patients' needs);To assess fatigue (pre- and post-intervention) and its evolution;To describe the QoL at baseline and after the intervention.

Although this is a feasibility study, patients participating in either program will benefit from a possible improvement in their fatigue status. There are no risks to report.

## Method and analysis

### Design

This is a prospective, single-center, randomized interventional feasibility study. This feasibility study proposes the implementation of two intervention programs (CBT and Hypnosis) to reduce CRF. Thus, patients included in the study will be randomized into two parallel groups (ratio 1:1). Procedure is detailed below. This research will use mixed methods (both quantitative and qualitative analyses) and data triangulation. Indeed, to increase the ecological validity of the study it is necessary to cross different types of data, analyses and/or participants (Salkind, 2010). In this study, combining a quantitative approach to program satisfaction with a qualitative approach to program experience allows us to answer complex research questions while taking advantage of the benefits and minimizing the limitations of qualitative or quantitative studies alone.

### Population

#### Recruitment

Patients will be included in a French regional anticancer center. We plan to include 60 patients who will be allocated to each intervention group [i.e., Hypnosis (*n* = 30) and CBT (*n* = 30)]. The sample size will not be based on a power analysis but on the estimated recruitment capacity in the cancer institute.^1^ A recruitment of 30 patients per intervention group would allow us to estimate in each group a proportion of at least 80% of patients adhering to each intervention, with their 95% confidence intervals, of amplitude 0.28 (Machin et al., 2009).

#### Eligibility

Inclusion criteria will be as follows:

1) Age ≥ 18 years2) WHO performance status ≤ 23) Progressive colorectal adenocarcinoma after first line metastatic chemotherapy4) Able to understand and read French5) Visual Analog Scale for fatigue ≥ 4: based on our previous work on metastatic CRC patients where 48% complained of moderate fatigue throughout treatment, and since our variable of interest is fatigue, we decided to include patients already fatigued (4/10 on VAS).6) Patients starting a second or third line of metastatic chemotherapy7) Patients who signed the informed consent8) Patients subscribed to a French Social Security system

The criteria for non-inclusion will be as follows:

1) Patients who do not have a telephone or devices that allow remote monitoring of sessions at home2) Presence of brain metastases3) Chronic pain evolving for more than 3 months and on morphine4) Patients who used to and/or have a regular and habitual practice in meditation, or in relaxation techniques such as yoga, hypnosis or sophrology5) Medical (neurological, psychiatric, etc.) or psychological conditions that do not allow participation in the protocol (filling out the questionnaires and the booklet, as well as following the sessions)6) Deaf patient without hearing aids7) Patient under guardianship or legal protection

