### Procedure

Three time points will be considered: T0 corresponds to the patient' inclusion in the study (patient agreement and completion of the study questionnaires), T1 corresponds to the end of the intervention after 6-weeks of intervention (semi-directive interviews on the acceptability of the program and completion of the questionnaires), and T2 corresponds to a follow-up visit 3 months after the intervention (questionnaires).

During the medical consultation with the oncologist, eligible patients will be identified. After oncologist approval, only inclusion/non-inclusion criteria (including fatigue VAS) will be retrieved by the investigator. If eligible, a patient will receive the information letter and consent, and will be asked to return it for cure of chemotherapy N°1 (T0).

The investigator will collect the sociodemographic (including the Score EPICES) and the medical variables. She/he will also present a web application (smartphone or tablet), available on AppStore or PlayStore (“*Mon Essai Patient*”) from the company Exolis. Patients who are not comfortable with these tools have the option of having a paper format. This application allows to collect every data from the questionnaires, encourages the daily or weekly assessment and limits missing data because patients will receive a notification when a questionnaire must be completed. Then a clinical research associate will give the different self-questionnaires to the patient, responding her/his questions if necessary. As shown Table 2, the patient will fill out, during ~30 min, the MFI-20, theQLQ-C30, and the VAS fatigue.

**Table 2 T2:** Measurements used in the study.

**Measures**	**Screening**	**T0**	**6 weeks interventions**	**T1**	**T2**
Inclusion/non-inclusion criteria	X				
Information letter and consent		X^a^			
Sociodemographics and medical variables		X		X^b^	
EPICES score		X^c^			
Fatigue and Quality of Life:					
6. VAS fatigue (physical/emotional)	X	X	X^c^ Daily assessment		X^c^
7. MFI-20		X^c^		X^c^	X^c^
8. QLQ-C30		X^c^		X^c^	X^c^
Feasibility					
9. SEQ			X^c^		
			Weekly assessment		
10. ISQ-8				X^c^	
11. Qualitative interviews				X^c^	

a *Information letter and consent are delivered at screening and retrieved if inclusion at T0*;

b * if progression, relapse or change of treatment*;

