**Figure 2 F2:**
[figure not shown]
Study design with two-arms randomization (hypnosis and CBT), 6 sessions each. Flexibility in terms of sessions is foreseen, i.e., a patient may have a session shifted by 1 or 2 weeks depending on its WHO performance status and/or the therapist's availability. This takes into account the toxicities, need to always have the same practitioner for the 6 sessions, and the reality of the field (absences, vacations, etc.).

At T1, after the interventions, patients will be asked to complete again the QLQ-C30, MFI, EVA fatigue and the ISQ-8 (see Table 2). They also will be interviewed by a trained psychologist about their acceptation of the program with semi-directed interviews. The interviews will be semi-structured to obtain as much information as possible. A first general question will ask about their general opinion of the program. Then, they will be asked to talk about their reasons for agreeing to participate in the program, as well as information about the implementation. Patients will answer whether the program seemed suitable or not and finally, whether they would recommend it to others. Each question will be as broad as possible, and then participants will be prompted if more detail is needed. Patients who would like to end their participation in the program prematurely will also be invited to participate in these interviews, as the reasons for non-adherence are among the evaluation criteria.

At the end, regardless of the inclusion arm, patients will receive one intervention over a period of 6 weeks and will be re-interviewed 3 months after the procedure (T2) on their level of fatigue and quality of life, representing 5 months involvement in total.

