### Statistical considerations

The primary outcome will be analyzed in each intervention group. The proportions of patients who adhered to each intervention program (Hypnosis and CBT) will be presented with their two-sided 95% confidence intervals (95% CI), as the proportion of patients giving consent to participate in the study among the eligible patients at the screening who were offered the study. All statistical analyses of the secondary criteria will be done by group. Categorical variables will be described by the number of observations (N) and the frequency (%). Missing categories will be counted. Quantitative variables will be described by the number of observations (N), mean, standard deviation, median, minimum, and maximum. In case of missing data no imputation method will be used.

For the comparison of qualitative variables, a chi-square test or a Fisher's exact test will be used if the theoretical number of observations is <5. For the comparison of quantitative variables, a Student's *t-*test or a Kruskal-Wallis test will be used. For comparisons between two time points a Wilcoxon test for paired samples will be used. The correlation between the VAS values for fatigue and the scores on the MFI-10 questionnaire will be studied using Pearson's correlation coefficient or Spearman's correlation coefficient. The evolution of VAS fatigue values over the course of treatment will be modeled using linear mixed models to account for the repeated nature of the measurements. The analysis of the QLQC-38 questionnaire will be performed according to the EORTC guidelines.

All statistical tests will be two-sided and the significance level is set at 5% (i.e., *p* < 0.05). Statistical analyses will be performed with STATA v16 software and a statistical report will be provided according to the current model.

Program satisfaction will be assessed on the basis of the CSQ-8 score, SEQ evaluation of each session and put into perspective with the individual semi-structured interviews analyzed with QDA Miner. This is a mixed methods and qualitative data analysis software developed by Provalis Research. The program was designed to assist researchers in managing, coding and analyzing qualitative data. QDA Miner was first released in 2004 and the latest version 6 was released in September, 2020.

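### Paired within-arm tests of fatigue change, in patients selected on fatigue VAS ≥ 4 and with no untreated arm, cannot separate program benefit from regression to the mean or the natural course

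*Protocol article*

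**What the plan says.** All places are in the protocol article.

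- **Entry rule (Eligibility, inclusion criterion 5):** fatigue VAS of 4 or more, because "since our variable of interest is fatigue, we decided to include patients already fatigued (4/10 on VAS".
- **When the selecting value is read (Procedure):** at screening, before T0: "After oncologist approval, only inclusion/non-inclusion criteria (including fatigue VAS) will be retrieved by the investigator". Table 2 schedules another VAS at T0. Its T1 cell for the VAS is blank, but the text after Figure 2 says that at T1 "patients will be asked to complete again the QLQ-C30, MFI, EVA fatigue and the ISQ-8".
- **Objective (Objectives):** "To assess fatigue (pre- and post-intervention) and its evolution".
- **Analysis (Statistical considerations):** "All statistical analyses of the secondary criteria will be done by group", and "For comparisons between two time points a Wilcoxon test for paired samples will be used". Tests are two-sided at 5%, and the VAS course is fitted with linear mixed models.
- **Control:** none. Every patient receives hypnosis or CBT.
- **Daily VAS (Repeated measures):** from T0 to T1, 49 assessments. T0 falls at chemotherapy course 1 and session 1 at course 2 (Procedure), with courses two weeks apart (Introduction).

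The article does not say which reading is the pre-intervention value. It mentions regression to the mean nowhere, including the limitations in the Discussion.

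**The concern.** Entry depends on a high reading of a variable that later serves as an outcome. A patient who passes the threshold on one fluctuating reading is, on average, above his or her usual level that day. All else being equal, later readings tend to be lower.

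A paired test within an arm asks whether the mean change is zero. With selection on the outcome and no untreated arm, zero change is not what doing nothing would necessarily produce. A low p-value in one or both arms could then be read as a sign that a program reduces fatigue, and could colour the hypotheses that the study is meant to generate for the later controlled trial.

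**Working it through.** **Inputs from the article.** Threshold 4 on a 0–10 scale; 30 patients per arm; two-sided 5%; T1 49 days after T0. The only precision figure is the 95% interval width of 0.28 for 80% adherence. It reproduces: Wilson for 24/30 is 0.627 to 0.905, width 0.278. It concerns adherence only and is not touched by this point.

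**Inputs that are assumptions.** Unselected VAS mean 3.5 to 4.5, SD 2.3; half the variance a stable patient level, half a daily state with day-to-day correlation r of 0.8 to 0.95; 3 to 14 days from screening to T0; no program effect and no time trend.

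**Formula.** For a normal variable selected at screening (S), let K = SD × φ(a)/(1 − Φ(a)), where a = (cut-off − mean)/SD.

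- Expected fall, S to T0: (1 − ρ(S,T0)) × K
- Expected fall, T0 to T1: (ρ(S,T0) − ρ(S,T1)) × K
- With half the variance stable: ρ at lag d = 0.5 + 0.5 × r^d

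If the VAS is recorded in whole points, a reading of 4 or more means a latent value of at least 3.5. At mean 3.5, a = 0 and K = 2.3 × 0.798 = 1.835.

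| Case (mean 3.5) | r^d at T0 | r^d at T1 | Fall S to T0 | Fall T0 to T1 |
|---|---|---|---|---|
| Mild: r 0.8, gap 14 d | 0.044 | 0.000 | 0.478 × 1.835 = 0.88 | 0.022 × 1.835 = 0.04 |
| Example: r 0.9, gap 7 d | 0.478 | 0.003 | 0.261 × 1.835 = 0.48 | 0.238 × 1.835 = 0.44 |
| Extreme: r 0.95, gap 3 d | 0.857 | 0.069 | 0.071 × 1.835 = 0.13 | 0.394 × 1.835 = 0.72 |

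**Simulated paired Wilcoxon tests (n = 30, no effect).** Chance of a significant fall in one arm; the nominal value in that direction is 2.5%.

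- T0 baseline: about 3% (mild), 16% (example), 43% (extreme).
- Screening baseline: about 60% to 68% in the example and extreme cases.
- In the example with a T0 baseline, at least one of the two arms shows it with probability 1 − 0.84² = 29%, against 1 − 0.975² = 4.9% nominally.

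**A second model** (trivariate normal; mean 3.5 to 5.0, SD 2.0 to 2.3) agrees in pattern. With mean 4, SD 2.3 and correlation 0.6 at every lag, the fall from screening to T1 is 0.4 × 1.835 = 0.73 points (50% false improvement), and the fall from T0 to T1 is nil (2% to 3%). With 0.8 between screening and T0 but 0.5 between screening and T1, the fall from T0 to T1 is 0.3 × 1.835 = 0.55 points (30%).

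**Sensitivity of the 16% example (T0 baseline).**

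- Natural rise of 0.3 points by T1: about 3% to 6%.
- Natural rise of 0.5 points: about 1% to 2%.
- 80% of the variance stable instead of half: about 9%.

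**Using the readings between T0 and session 1.** Two weeks of daily readings as baseline cut the example bias from −0.44 to about −0.17 points and false improvement from 16% to about 6%. A check that took the plain mean of 14 daily readings gave −0.23 points and 9%. Either way the bias shrinks but remains.

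**The case against.** The strongest reply has five parts.

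1. **The baseline is not the selecting reading.** T0 is a separate VAS. If fatigue does not carry over from screening to T0, or the correlation does not decay with time, the bias from T0 to T1 is nil. This stands, and it is why the range starts at the nominal level. However, the article does not fix T0 as the pre-intervention value, and fatigue states that last days or weeks would leave part of the bias.

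2. **Fatigue may rise.** These patients have progressed and are starting second- or third-line treatment. The Introduction calls progression and further treatment aggravating factors, and the Discussion cites an increasing-fatigue profile (11.83%). A reader might infer that patients must drift downward, or that the zero-change null is false by selection alone. The documents do not support that, because the net direction is unknown. An unknown natural course still leaves the within-arm p-value uninterpretable.

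3. **There is an untreated run-in.** A reader might infer that nothing in the design could reveal the drift. That overlooks about two weeks of daily VAS between T0 and session 1 in both arms. The planned mixed model does not single this period out, but the data are collected.

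4. **Fatigue is secondary in a feasibility study.** Adherence is primary and efficacy is left to a three-arm controlled trial. A reader might infer that the within-arm change will supply that trial's effect size, but no section says so. The Discussion does expect to learn which program is most effective. That is a comparison between arms selected alike, so this bias does not distort it.

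5. **The Wilcoxon sentence is generic.** True, and the detailed choice of contrasts may sit in an analysis plan not shown. But the pre/post fatigue objective is its obvious use, and the article itself fixes the entry rule, the analysis by group, the paired test and the 5% level.

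**Conclusion.** The point holds as a limit on interpretation. Paired within-arm tests of fatigue change cannot separate program benefit from regression to the mean or from the natural course under chemotherapy.

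The size is uncertain because the documents give no VAS mean, SD or retest correlation. Under the stated assumptions, with stationary fatigue and a T0 baseline, the false-improvement rate per arm runs from about 2.5% to about 43%. It is higher from a screening baseline, and lower or absent with a natural rise.

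The adherence endpoint, its sample size and all between-arm comparisons are unaffected. MFI and QLQ-C30 are affected less than the VAS, because patients are not selected on them directly. No size was computed for those scales. The change is worth making, but it does not threaten the study's main purpose.

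**What to change.** In Statistical considerations:

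1. Report within-arm change in fatigue with 95% confidence intervals as descriptive, without paired-test p-values. State that it may include regression to the mean from the VAS entry rule.
2. Confine hypothesis tests of fatigue change to the between-arm difference.
3. State that the screening VAS is never the baseline. For the daily VAS, use the readings between T0 and session 1 as the pre-program baseline, or give them their own segment in the mixed model. This reduces the bias but does not remove it.

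Do not present the change from screening to T0 as a gauge of the remaining drift. The two falls are complementary parts of one total. In the table above, the fall before T0 is smallest (0.13) when the fall after T0 is largest (0.72), so a small early change would reassure exactly when it should not.

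The cost is wording only, using data already scheduled. The downside is that no within-arm p-value can be quoted.
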